## Abstract

**Background:**

Parastomal hernia is a common complication of an enterostomy and can have a significant impact on health-related quality of life. Currently used methods of repair have high recurrence rates and considerable risk for complications. We have developed a new technique for parastomal hernia repair that uses full-thickness skin graft as reinforcement.

**Methods:**

This study protocol describes a multicentre randomised controlled trial on parastomal hernia repair comparing a new full-thickness skin graft technique with conventional synthetic composite mesh as reinforcement of the abdominal wall. Patients with a symptomatic parastomal hernia will be included and followed up at 3, 12 and 36 months, with surgical complication as the primary outcome. Secondary outcomes will be recurrence rate and health-related quality of life assessed with VHPQ, EORTC C30 and CR29. Tissue biology and collagen metabolism will be investigated pre- and postoperatively using biopsies of the abdominal wall fascia and blood samples.

**Discussion:**

Parastomal hernia constitutes a major clinical problem where the prospects of a good result after hernia repair are presently poor. This new method of repair with full-thickness skin grafting could be a new alternative in our surgical toolbox, but before then, it must be evaluated properly.

**Trial registration:**

ClinicalTrials.gov NCT03667287. Registered on September 12, 2018

## Administrative information

Note: the numbers in curly brackets in this protocol refer to SPIRIT checklist item numbers. The order of the items has been modified to group similar items (see http://www.equator-network.org/reporting-guidelines/spirit-2013-statement-defining-standard-protocol-items-for-clinical-trials/).

## Introduction

### Background and rationale {6a}

Parastomal hernia is the main complication of an enterostoma [1–3]. Occurrence rates up to 80% have been reported, with numbers varying considerably due to differences in diagnostic method, follow-up time, type of stoma, and the lack of a uniformly accepted definition of parastomal hernia [2–5]. Symptoms from a parastomal hernia range from asymptomatic to problems significantly impairing the patient’s quality of life, even life-threatening due to strangulation of the hernia content. There are few studies investigating the frequency of specific complaints, and there is thus little information clearly indicating which patients are likely to benefit from surgical repair [6].

Several techniques are presently used for parastomal hernia repair. The European Hernia Society recommends a synthetic mesh plasty, but scientific evidence on how and in what position the reinforcing material should be applied is weak. Even the best available methods today are associated with high recurrence rates and significant risk for complications that can be fatal [7–9]. The use of synthetic mesh material is associated with severe complications such as mesh infection, fistula formation and erosion of the intestines [9]. There are also patient associations and other communities that oppose the use of synthetic mesh material (https://www.facebook.com/groups/meshproblems/, https://www.facebook.com/MeshMeNot/, https://meshmenot.wordpress.com/, https://meshvictimsunited.org/).

Autologous full-thickness skin grafting (FTSG) has been shown to be a possible alternative to conventional synthetic mesh in hernia repair [10]. By avoiding the use of foreign materials, FTSG could offer safer and less expensive reinforcement in parastomal hernia repair. The technique of grafting autologous skin in hernia repair was successfully used before the advent of synthetic mesh, but its application in parastomal hernia is new [11, 12].

The present RCT follows a translational chain of research starting with a murine model which showed good FTSG survival in both intraperitoneal and onlay positions [13]. Furthermore, in an experimental model, fresh FTSG was shown to have equal or better tensile strength than both synthetic and biological reinforcement material, which is a prerequisite in hernia surgery [14].

The study intervention was developed with the aid of 3D-models reconstructed from computerised tomography (CT) scans of patients suffering from parastomal hernia. Four pilot patients have then been operated on in a feasibility study which showed no procedure-related complications [15].

### Objectives {7}

The objective of the trial is to compare a novel method of repair for parastomal hernia to one of the best available conventional methods in terms of surgical complications, recurrence, QoL and health economics.

Our hypothesis is that autologous FTSG as reinforcement material in parastomal hernia (PH) repair offers a safer and more comfortable alternative to conventional synthetic mesh material.

### Trial design {8}

The trial is a parallel group, superiority trial with an allocation ratio of 1:1.

## Methods: participants, interventions and outcomes

### Study setting {9}

This study will initially take place at three public hospitals in Sweden, one university hospital, one regional hospital and one county hospital, all situated in the north of Sweden. The university hospital is a tertiary referral centre for advanced abdominal wall reconstructive surgery.

### Eligibility criteria {10}

Consultant surgeons with long experience in abdominal wall surgery will be responsible for the assessment of potential study participants before inclusion and will attend all intervention procedures.

Inclusion criteria:
Colo-, ileo- or urostomyParastomal hernia diagnosed with intrastomal ultrasonography and/or CT-scanSymptoms from the parastomal hernia requiring surgical intervention18 years of ageSufficient knowledge of the Swedish language assuring that questionnaires can be adequately understood and answered

Exclusion criteria:
Cognitive impairment causing poor compliance to postoperative prescriptions and/or answering questionnairesInsufficient amount of good quality skin suitable for transplantationExpected high donor-site morbidityFistula/e adjacent to stomaMb CrohnConcomitant ventral hernia requiring mesh repairOther intra-abdominal disease requiring surgical intervention

### Who will obtain informed consent? {26a}

Information about the trial will be given to potential study participants per telephone or in person by the assessing surgeon or other responsible researcher. The potential candidate will then be assessed in the out-patient clinic by a surgeon regarding inclusion and exclusion criteria. If the potential study participant is eligible for inclusion, written and verbal informed consent will be obtained at the time of assessment after relevant questions have been answered. The potential study participant may also be given time for consideration and submit their consent at a later date.

### Additional consent provisions for collection and use of participant data and biological specimens {26b}

Patients included in the study will also be offered the opportunity to participate in an ancillary study investigating tissue biology of patients with parastomal hernia. Consent for participating in this ancillary study will be obtained in conjunction with acquisition of consent for the main study.

For more information, see the “Plans for collection, laboratory evaluation, and storage of biological specimens for genetic or molecular analyses for this trial/future use {33}” section.

## Interventions

### Reasons for the choice of comparators {6b}

There is weak evidence as to which method of repair is the best available at present. The European Hernia Society is against the use of suture repair as well as repair using a biological mesh [16]. In terms of recurrence, there is evidence favouring IPOM mesh using the Sugarbaker technique, but evidence is weak regarding morbidity.

In view of the fact that there is such weak evidence on how synthetic mesh should be applied to obtain the best results, our comparator was chosen for its similarity to the experimental intervention [15].

2.Synthetic mesh as reinforcement. A midline laparotomy is performed and adhesiolysis around the stoma is performed if necessary. The stoma is dissected free at the mucocutaneous junction, sealed with a temporary suture and retracted into the abdomen. The fascial defect is then reduced to appropriate size depending on the size of the patient’s stomal intestine with interrupted single 2-0 PDS (Ethicon Inc. Cornelia, GA, USA). A DynaMesh®-IPST (FEG Textiltechnik mbH, Aachen, Germany) of appropriate size is then applied to the stomal intestine. The stoma is brought up through the reduced fascial defect, and the DynaMesh® is sutured to the peritoneum and abdominal wall with interrupted 2-0 PDS sutures at intervals of 10–20 mm along the edges of the graft. Reinforcing sutures are also placed over the fascial reduction so that the forces in the abdominal wall are transferred from the fascial reduction to the mesh.

### Criteria for discontinuing or modifying allocated interventions {11b}

Any study patient requesting to end their participation in the study will immediately be withdrawn from whatever stage they have reached in the study process without having to explain why.

The anatomy in the abdominal cavity as well as the current conditions at the time of surgery can prevent the feasibility of the planned procedure, in part or completely. Minor alterations to the surgical interventions may be accepted, such as isolated deviations from the specified intervals when suturing the reinforcement material to the abdominal wall. Major obstacles that make the planned procedure impossible to perform without significant risk, such as massive adhesions or other contraindications such as finding disseminated malignancy, will exclude the patient from further participation in the study.

### Strategies to improve adherence to interventions {11c}

It is a great challenge to standardise surgical procedures in detail, since difficulty increases with the complexity of the procedure and the target organ for the surgical intervention.

Thorough operation manuals with clarifying pictures have been prepared with step-by-step guidance of procedural details. When additional study centres are included, a surgeon responsible from one of the initially participating centres will assist at the first operations to further assure standardisation and procedural adherence.

Any inherent variability of the procedures remaining, such as different surgeons having different approaches for exposure and dissection, will increase the external validity of the study.

### Relevant concomitant care permitted or prohibited during the trial {11d}

No other intra-abdominal interventions are permitted concomitant to the planned intervention. Potential iatrogenic injuries which occur during the intervention should be managed according to surgical standards. Minor mid-line hernias which allow for suture repair can be managed during the intervention, but if requiring mesh reinforcement, the patient cannot be included in the study.

### Provisions for post-trial care {30}

Should any study participant suffer harm, he/she is entitled compensation under the Swedish Patient Injury Act. Since the study surgical intervention and all postoperative care is performed under the Swedish public healthcare system, all study participants will be covered by the Swedish regional health authorities mutual insurance company (Löf) [17].

## Outcomes {12}

### Participants will be followed up at 3, 12 and 36 months postoperatively.

#### Primary outcome:

Rate of surgical complications at 3, 12 and 36 months. Complications will be assessed over a 3-year period at regular follow-ups by an independent surgeon who is unaware of which surgical method was used. Eventual complications include infection, bleeding, seroma, and fistula formation. Regarding recurrence, the best available methods of repair today are associated with complications that in some cases can be fatal [7].

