#### Rate of complications and recurrences

Data are presented descriptively and the results from each study group are compared with chi-squared test.

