### Interim analyses {21b}

After 30 operations have been performed, a safety analysis is performed. It is conducted by a scientifically experienced researcher (at least assistant professor) with long clinical experience of abdominal wall surgery but has no connection with the study. The safety analysis is based on CRF data and complications graded Clavien-Dindo 3b or worse based on information from copies of the medical records from postoperative care on the ward and clinical follow-ups. Should serious or unexpected complications associated with study allocation arise, the study will be interrupted by the surgeon performing the safety analysis. Safety analysis data will otherwise not be available to the responsible researchers or surgeons participating in the study.

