## Discussion

Despite the relative frequency of parastomal hernia, there is a considerable lack of knowledge regarding epidemiology, symptomatology, indication for surgery and best practice when surgically managing the condition [1–3, 6]. The European Hernia Society guidelines on prevention and treatment of parastomal hernia provide predominantly weak evidence for both the epidemiological aspects of the disease and its subsequent treatment [16]. Since there is a general lack of studies comparing different techniques for parastomal hernia repair, there is no consensus on what the best method available is. This makes the design of a trial, and in particular, choosing a comparator to evaluate a novel treatment, difficult and even controversial. Our choice of using reinforcement with DynaMesh®-IPST as a comparator was made because of its similarity to our FTSG-method and with the background of recurrence rates in the vicinity of other IPOM methods [22]. Furthermore, recurrence of a parastomal hernia after surgical repair is of minor importance compared to the serious and sometimes fatal complications of repair methods using synthetic mesh as reinforcement. The primary goal of benign surgery must be the safety of the patients, which the primary outcome of this trial.

Both methods investigated in this trial are open techniques despite the increasing number of colorectal interventions being performed laparoscopically. This is primarily because it is not possible to apply an FTSG to the abdominal wall using conventional laparoscopic tacks. Therefore, to avoid cyst formation, an open technique with better control over the sutures was considered safer for the patients given the importance of the FTSG application under tension.

An advantage of using FTSG is that this reinforcement material is usually readily available in the quantity required. FTSG has been shown to be a safe and potentially useful alternative in giant incisional hernia repair [10, 23].

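### The safety hypothesis rests on serious mesh complications, but the primary outcome is ungraded and no between-arm comparison of serious complications is prespecified

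*Protocol article*

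**What the plan says.** - **Hypothesis.** Objectives {7} states that the graft "offers a safer and more comfortable alternative to conventional synthetic mesh material". Trial design {8} makes this a superiority comparison.
- **Rationale.** The Discussion ranks recurrence below the "serious and sometimes fatal complications of repair methods using synthetic mesh as reinforcement" and gives patient safety as the reason for the choice of primary outcome. Background and rationale {6a} names mesh infection, fistula and bowel erosion.
- **Primary outcome.** Outcomes {12} defines it as "Rate of surgical complications at 3, 12 and 36 months" and adds: "Eventual complications include infection, bleeding, seroma, and fistula formation". No grade or weight is attached.
- **Analysis.** For complications and recurrences: "Data are presented descriptively and the results from each study group are compared with chi-squared test".
- **Secondary outcomes.** Recurrence, pain, quality of life and health economics. Complications enter only as a cost item.
- **Grading.** Interim analyses {21b} bases the safety analysis after 30 operations on CRF data and "complications graded Clavien-Dindo 3b or worse based on information from copies of the medical records". Unless the study is interrupted, these data do not reach the trial's researchers or surgeons.
- **Data collected.** Plans for assessment and collection of outcome data {18a} has the blinded follow-up surgeon record surgical complications as seroma, infection or other, and also readmission or reoperation. Reporting adverse events and harm {22} puts complications in the medical records and the CRF.

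**The concern.** The harms that motivate the trial are severe, whereas the outcome that tests the hypothesis does not separate severe from minor. A seroma and a fistula count alike. Two kinds of misreading follow. A difference made up mostly of seromas could be reported as showing that the graft is safer, with no prespecified estimate for the harms behind the claim. Conversely, a real reduction in serious events could be masked by minor wound events of similar frequency in both arms.

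The protocol treats grade 3b or worse as the relevant measure when deciding whether the trial is safe to continue, but plans no final comparison on it. If a severity analysis is added only once results are known, by analysts whom Who will be blinded {17a} describes as unblinded, it will be open to the charge of being data-driven.

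**Working it through.** **1. The plan's own figure.** Inputs from Sample size {14}: 15% vs 40%, 80% power, 39 per arm, 45 per arm enrolled. The significance level is 0.05. Pooled formula:

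n = [z_α √(2·p̄·q̄) + z_β √(p₁q₁ + p₂q₂)]² / (p₁ − p₂)²

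with p̄ = 0.275, so √(2 × 0.275 × 0.725) = 0.6315 and √(0.1275 + 0.24) = 0.6062.

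- One-sided: (1.645 × 0.6315 + 0.842 × 0.6062)² / 0.0625 = 38.4, so 39. This matches the protocol.
- Two-sided: (1.960 × 0.6315 + 0.842 × 0.6062)² / 0.0625 = 48.9, so 49.

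The sidedness is a separate matter. What counts here is that the sample size rests wholly on the ungraded rate.

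**2. Can the primary result and serious harm diverge?** The protocol gives no rate of serious complications, so the serious-event rates below are assumptions. Power is by exact binomial enumeration with 45 per arm, two-sided 0.05, chi-squared without continuity correction. The rate is taken as patients with any complication, which the chi-squared test suggests but the text does not state.

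| Scenario | Any complication, graft vs mesh | Primary significant | Serious, graft vs mesh (assumed) | Serious comparison significant |
|---|---|---|---|---|
| (a) | 15% vs 40% (protocol's rates) | 78% | 10% vs 10% | 6% |
| (b) | 35% vs 40% (assumed) | 8% | 5% vs 20% | 63% |

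These splits were chosen to separate the two endpoints. In (a), serious events are 10/15 = two thirds of graft complications but 10/40 = a quarter of mesh complications. In (b), they are 5/35 = one seventh and 20/40 = a half. They show that divergence is possible, not that it is likely.

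**3. What a graded secondary could deliver.** Half-width of the 95% CI = 1.96 √(p₁q₁/45 + p₂q₂/45). For 5% vs 20%: 1.96 √(0.0475/45 + 0.16/45) = 1.96 × 0.0679 = 13.3 points.

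| Serious, graft vs mesh (assumed) | Half-width, points | Power, chi-squared | Power, Fisher |
|---|---|---|---|
| 5% vs 10% | 10.8 | 16% | 6% |
| 3.75% vs 10% (a quarter of 15% vs 40%) | 10.4 | 24% | 9% |
| 5% vs 15% | 12.2 | 39% | 23% |
| 7.5% vs 20% (half of 15% vs 40%) | 14.0 | 43% | 30% |
| 5% vs 20% | 13.3 | 63% | 48% |

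If serious events are a fixed quarter to half of the planned rates, power is about 24% to 43%. The graded outcome therefore belongs among the secondaries, as an estimate.

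**The case against.** **The trial could still describe serious harm.** A reader might infer that it cannot say whether serious complications differ, or that the chi-squared test is the only analysis planned. The documents do not support either. Reoperation, readmission and complication type are recorded at follow-up, events enter the CRF and medical records, and descriptive presentation is promised. The safety analysis already relies on grades drawn from such sources. This objection stands and limits the point to the missing prespecified comparison. It also shows that the fix is feasible.

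**The article is condensed.** A full protocol or analysis plan, not shown, may contain grading rules and severity tables. That is fair for detail. However, the article does set out its primary outcome, its secondary outcomes and its follow-up variables, and it names Clavien-Dindo for the safety analysis alone. The mismatch is between the stated rationale and the stated outcomes.

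**A safety trigger and a final comparison serve different purposes.** True, and there is no contradiction in using different measures. The gap in support for the hypothesis remains.

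**The illustration is selective.** This stands. The serious-event rates are assumed, the two scenarios are favourable to the point, and Fisher's test gives lower power.

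**Grade 3b does not match the named harms.** A fistula or mesh infection can fall below that cut. This stands, and is why a display by type is needed beside the graded proportion.

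**Conclusion.** The point holds in a limited form. The safety hypothesis is motivated by serious mesh complications, the primary outcome ignores severity, and no serious or graded complication outcome is prespecified for the final comparison. The primary outcome remains valid for what it measures, but a positive result alone would not show that the harms motivating the trial are reduced, because minor events could produce it.

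The size of the problem cannot be fixed from the documents, since they give no serious-event rate. Over assumed rates of 10% to 20% with mesh and about 4% to 7.5% with the graft, 45 per arm gives an interval half-width of about 10 to 14 points and power of roughly 16% to 63% by uncorrected chi-squared. Losses to follow-up would lower the precision further. This is a worthwhile, inexpensive improvement and not a flaw that invalidates the design.

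**What to change.** Leave the primary outcome and its sample size as they are, and make these changes.

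1. Add to the secondary outcomes the proportion of patients with any Clavien-Dindo grade 3b or worse complication through each follow-up (3, 12 and 36 months), reported as a risk difference with 95% CI. The cut is the one already used at the safety analysis.
2. Present complications per arm by type, with fistula and mesh infection as categories of their own, and by worst grade per patient.
3. Assign grades from the CRF and medical records, using text that does not reveal the reinforcement material, so that the follow-up surgeon stays blinded even after a reoperation.
4. State that any conclusion that the graft is safer will be reported together with the graded estimate.

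**Cost.** One grade field on the CRF, finer complication categories, some work to mask record extracts, and a small number of extra analyses. The main drawback is limited precision: the interval will often be compatible with no difference, so the result should be presented as an estimate and not as a test. Trial status describes recruitment as current, with completion aimed for by the end of 2025 and follow-up to 36 months after surgery. The addition should be dated and made before outcome data are compared by arm.

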#### Secondary outcomes:

Recurrence. Parastomal hernia recurrence will be assessed clinically, with stomal ultrasound and/or CT-scan.Pain. All subjects will complete the Ventral Hernia Pain Questionnaire (VHPQ) to assess and compare preoperative pain ratings related to daily activities with ratings at all clinical follow-ups [18].Quality of life. All subjects will complete the European Organisation for Research and Treatment of Cancer questionnaire module for colorectal cancer (EORTC CR29) as well as the European Organisation for Research and Treatment of Cancer core quality of life questionnaire (EORTC QLQ-C30) to assess and compare different aspects of quality of life pre- and postoperatively at all clinical follow-ups [19–21].Health economics. Cost-effectiveness for each treatment arm. The total cost of each method will be calculated from the hospital healthcare costs system based on duration of surgery, cost of operating time and equipment, duration and cost of anaesthesia and cost of complications including infection, bleeding, seroma and fistula formation.

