## Data collection and management

### Plans for assessment and collection of outcome data {18a}

All clinical study data will be registered in an Access® database (Microsoft, Redmond, WA, USA).
Baseline data are collected at the time of inclusion once assessment of eligibility by the including surgeon is complete. At this point, the surgeon is unaware of what intervention the patient will be allocated. Baseline data include:
BMI. Body mass index.ASA (American Society of Anesthesiologists) class.Current medical conditionsCurrent medicationNumber and type of previous abdominal surgeries.Type of and reason for stomaOperation data will be collected immediately after surgery by the surgeon. Data collected on completion of surgery:
Participating surgeonsTreatment allocationSize of the hernia defect before and after reductionSize of the FTSGLength of stoma bowel above the fasciaOperating timeMinimum overlap of reinforcement materialData on postoperative care on the ward will be collected by the blinded nursing staff on a case report form (CRF). After discharge, the CRF will be collected and registered in the database. Parameters monitored daily during the entire time on the ward:
C-reactive proteinSerum albuminComplete blood cell countSerum creatinineBlood glucoseOxygen saturationExperienced pain assessed on a visual analogue scaleClinical follow-up data will be collected by the blinded surgeon conducting the follow-up. This surgeon will be experienced in stoma surgery (i.e. colorectal, or abdominal wall surgery) but will not receive any specific training on the follow-up procedure in this study. Parameters that will be assessed at the clinical follow-up:
BMIClinically judged recurrenceSurgical complication (seroma, infection, other)Stoma complication (stenosis, necrosis, other)Readmission or reoperation during the follow-up periodPain assessed on a visual analogue scaleExperienced improvement assessed on a visual analogue scaleAbnormal healing process or poor aesthetic result of the operation scarCompliance to the postoperative girdle prescribedQuestionnaires both preoperative and during the follow-up period will be collected by the research group administrators and stored in a separate Access database. Questionnaires used in the study are:

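### The health-economic 'total cost' is built from a list that omits the index ward stay, readmissions not caused by a complication, and reoperation for recurrence

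*Protocol article*

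**What the plan says.** Objectives {7} sets out to compare the two repairs "in terms of surgical complications, recurrence, QoL and health economics". Under Secondary outcomes, the economic outcome is "Cost-effectiveness for each treatment arm", and its cost side is then specified as a list. It begins: "The total cost of each method will be calculated from the hospital healthcare costs system based on duration of surgery, cost of operating time and". After naming equipment, it closes with anaesthesia and complications: "duration and cost of anaesthesia and cost of complications including infection, bleeding, seroma and fistula formation".

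The Statistical methods section on health economics adds descriptive presentation and a between-arm Mann-Whitney or t test. It does not widen the cost definition.

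Three other places bear on the point:

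- The primary outcome illustrates complications with the same four items: "Eventual complications include infection, bleeding, seroma, and fistula formation".
- Recurrence is a secondary outcome of its own: "Parastomal hernia recurrence will be assessed clinically, with stomal ultrasound and/or CT-scan".
- Section {18a} lists readmission or reoperation among the follow-up data, and describes a daily ward record: "Parameters monitored daily during the entire time on the ward".

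**The concern.** The label and the list do not match. A total cost would normally include the days spent on the ward after an open laparotomy and any later operation for the same condition. Neither is in the list. Recurrence is classed apart from complications, so the complication item does not clearly bring re-repair in either.

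A cost left out of both arms cancels only if both arms incur it equally. Otherwise the arm that uses more of it looks cheaper than it is. Unequal use is plausible here: the arms differ in reinforcement material and one involves harvesting skin, so length of stay or later re-repair could differ. The documents do not say that they will. At stake is the answer to one stated objective, health economics. The primary outcome, the sample size and the safety review are unaffected.

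**Working it through.** The plan states no cost, length of stay, readmission rate, recurrence rate or expected cost difference, so there is no figure to reproduce. The check compares the cost list with the outcomes and the data collected, and then gives an illustration under stated assumptions.

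**Step 1. Which items are in the cost list?**

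| Item | In the cost list? | Collected or derivable under {18a}? |
|---|---|---|
| Surgery duration, operating time | Yes | Yes, operating time |
| Equipment, anaesthesia | Yes | From the hospital cost system |
| Complications, and the stay, readmission or reoperation they cause | Yes, on a natural reading of an open-ended item | Yes |
| Index ward stay without a complication | Not named | Yes, days can be derived from the daily ward record |
| Readmission not caused by a complication | Not named | Yes, on the follow-up form |
| Reoperation for recurrence | Not named | Yes, reoperation is on the follow-up form |

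**Step 2. Could re-repair come in through the complication item?** Three places point against it. Recurrence has its own entry under Secondary outcomes. It is not among the four examples given for complications, either in the primary outcome or in the cost list. The follow-up form in {18a} records recurrence as an item separate from surgical complications and from stoma complications.

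**Step 3. Direction of the error.** Let D be the difference in mean counted cost (arm A minus arm B). Let C be the cost of one repair, d the excess recurrence risk in arm B, s the share of recurrences that are re-repaired, L the excess uncomplicated ward days in arm B and w the cost of a ward day. Leaving aside readmissions without a complication:

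full difference = D − (d × s × C) − (L × w).

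The plan reports D alone. If d or L is positive, D flatters arm B. The sign would reverse only if D is positive and d × s × C + L × w exceeds it. Nothing in the documents fixes D, d, s, L, C or w, or says which treatment would be arm B.

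**Step 4. Illustrative size of the re-repair term.** Assumptions, none from the documents: a re-repair costs C, about the same as an index repair; d is 5 to 30 percentage points; s is 25% to 100%. The entries are d × s, in units of C per patient.

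| d | s = 25% | s = 50% | s = 100% |
|---|---|---|---|
| 0.05 | 0.0125 | 0.025 | 0.05 |
| 0.10 | 0.025 | 0.05 | 0.10 |
| 0.20 | 0.05 | 0.10 | 0.20 |
| 0.30 | 0.075 | 0.15 | 0.30 |

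For the 39 patients per arm in the power calculation, this is 39 × 0.0125 = 0.5 up to 39 × 0.30 = 11.7 uncounted extra repairs in the arm that recurs more. Ward days would add to or offset this; no range is given for them because the documents offer nothing to anchor one.

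**The case against.** Much can fairly be said on the other side.

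- **Open-ended wording.** The complication item says 'including', and the follow-up form has an 'other' category for both surgical and stoma complications. A reader might infer that the plan leaves out hospital stay and readmission altogether, or costs only four complication types. The text does not support that. Bed days, readmissions and reoperations caused by a complication can be counted as written. This stands, and it limits the gap to the three items in the heading.
- **Condensed article.** Costing detail is commonly left to a full protocol or a health-economic plan. This weakens the point but does not remove it: the article is not silent, since it gives a component list and calls the result total cost.
- **Recurrence is still reported.** It appears by arm as its own outcome and could serve as the effect measure in a cost-effectiveness ratio. However, no such ratio is defined, and reporting recurrence does not put the cost of re-repair into the cost comparison.
- **Importance of recurrence.** The Background calls recurrence rates high, but the documents do not call recurrence the main driver of later cost. The Discussion ranks it well below the serious complications of mesh repair. That is a safety judgement and does not make a re-repair free. Equally, not every recurrence leads to an operation, which is why the share s is varied above.
- **The cost claim.** A reader might infer that the trial sets out to prove the skin graft cheaper. The Background says only that "FTSG could offer safer and less expensive reinforcement in parastomal hernia repair", a tentative remark, and the stated hypothesis concerns safety and comfort. Health economics is nevertheless a stated objective, so the comparison should be sound whichever arm it favours.

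**Conclusion.** The point holds in limited form. As written, the total cost does not include the uncomplicated index stay, readmissions not caused by a complication, or reoperation for recurrence. If the arms differ in these, the comparison is biased towards the arm that uses more of them.

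The bias is conditional, and its size and direction are unknown. The range of 0.0125 to 0.30 of one repair's cost per patient rests entirely on assumed recurrence differences, re-repair shares and equal repair costs, and it covers re-repair only. A reader might go further and infer that the plan will make the skin graft look cheaper, or that the cost conclusion would change sign. Neither can be shown: there is no mesh price, theatre cost, length of stay or recurrence rate to work from. This is a cheap improvement to a secondary outcome.

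**What to change.** In Outcomes {12}, Health economics, define total cost per patient as all hernia- or stoma-related hospital cost from index admission to 36 months. Keep the present components and add index ward days, all related readmissions, and any related reoperation including one for recurrence. Draw the costs from the same hospital cost system in both arms, and identify the events from the ward, readmission and reoperation data already collected under {18a}.

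If the wider extract is not wanted, rename the measure 'procedure and complication cost' and draw no total-cost or cost-effectiveness conclusion from it.

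The change costs a revised sentence and a wider extract from a system already in use. The small downside is having to judge which admissions are related to the hernia or stoma. That judgement should be made blind to allocation where possible. Because {17a} states that the data analysts are not blinded, it is better given to someone who is, such as the follow-up surgeon.
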